#### Selection of pharmacists

Pharmacists who work in the selected community pharmacies will be eligible to participate if:

They are currently registered by the Australian Health Practitioner Regulation Agency.Satisfactorily complete a Continuing Professional Development (CPD)-accredited online training course and assessment.Agree to follow procedures outlined in the trial protocol.Demonstrate competency in the use of POCT testing using the device supplied for the trial (intervention group).

The content for the CPD online training course, which is accredited by the Pharmaceutical Society of Australia, was developed by the research team for online delivery through Medcast. The online training consists of three or four self-directed eLearning modules depending on the study arm: (1) trial overview; (2) identification and enrolment of participants; (3) pharmacy-led CKD screening using QKidney risk assessment tool and POCT; and (4) QUM service. Pharmacists in both the intervention (will take all four modules) and control (modules 1–3) groups will be required to complete an assessment at the end of online training, which comprises multiple choice questions and requires an 80% pass mark to obtain a certificate of completion. Pharmacists can claim up to 5 CPD points, with the possibility of claiming additional CPD points for the time spent on conducting services related to the trial. The online learning modules will be evaluated to explore pharmacists’ experience and overall level of satisfaction, the relevance of the training to their practice and whether the stated learning objectives were achieved.

Pharmacists in the intervention group will receive additional training on the POCT (performed using Nova Statsensor Creatinine Meter or Nova Max Pro Creatinine and eGFR Meter, Nova Biomedical, Waltham, Massachusetts, USA),^36^ devices approved for use by the Therapeutic Goods Administration (online supplemental appendix 2). The analyser in these devices uses a finger prick sample of whole blood (1.2 µL) to measure creatinine within 30 s. In-built software then allows calculation of the eGFR or estimated creatinine clearance via the CKD Epidemiology Collaboration or Cockcroft-Gault equations. Such POCT devices are used to determine kidney function used in radiology and cardiac catheterisation services to minimise risk of contrast-induced nephropathy as well as in oncology and emergency departments to expedite patient care. They have also been used in emergency and community pharmacy settings for detection of nephrotoxic medications.^28 37^ All participating pharmacies will receive the online training modules specific to the intervention group including on POCT and are expected to demonstrate competence in obtaining the blood sample using the device.

10.1136/bmjopen-2023-079110.supp2Supplementary data

#### Selection of participants eligible for screening

Participants who are eligible for screening must:

Be between the age of 35 and 74 years.Be at an increased risk of developing CKD due to one or more of the following parameters: ≥60 years of age, hypertension, diabetes, established cardiovascular disease, obesity (body mass index (BMI) ≥30 kg/m^2^), current or former smoker, family history of kidney disease, prior acute kidney injury, Aboriginal & Torres Strait Islander origin.Not have kidney failure or not be receiving kidney replacement therapy.Not have a terminal illness.Not be pregnant.Be able to make independent decisions about their health.

Eligibility will be determined based on self-report by the prospective screening participant and based on the pharmacist’s judgement of the participant being able to make independent decisions about their health.

## Clinical protocol and recruitment procedure

The clinical protocol for the trial is summarised in figure 1, which illustrates each of the steps involved in recruitment, screening, QUM service and referral to GP. Promotional materials including flyers, posters and eligibility card for self-assessment will be provided to each participating pharmacy. Each pharmacy will assign one person to serve as the study champion, while all pharmacy staff members, including pharmacists, pharmacy interns and pharmacy assistants and technicians will be encouraged to support the recruitment. The expected duration of the participant recruitment is 6 months per pharmacy. The POCT kit in the intervention group pharmacies will be rotated across pharmacies over 12 months to ensure each pharmacy has at least 6 months to recruit 30 participants.

**Figure 1 F1:**
[figure not shown]
Procedures of recruitment of participants. BP, blood pressure; CKD, chronic kidney disease; CrCL, creatinine clearance; eGFR; estimated glomerular filtration rate; GP, general practitioner; NSW, New South Wales; POCT, Point-of-Care Testing; PSA, Pharmaceutical Society of Australia; QUM, quality use of medicines; SCr, serum creatinine; SMS, short messaging service; VIC, Victoria.

Screening participants will be recruited through the targeted community pharmacies. The recruitment process involves the pharmacists discussing the study and confirming participant eligibility. The pharmacist will manage potential participants using a purpose-built online software application hosted on a cloud-based server at The University of Sydney. This will ensure the integration of the recruitment process, including the delivery of intervention into the pharmacy recording platform and thereby automate key processes, such as risk assessment, medication history taking, referral letter production and follow-up. Also, direct storage of data in the cloud server will ensure no data are lost due to any systemic issues arising from individual pharmacies.

Following identification of screening participants, those who are eligible and willing to participate will be provided with the participant information statement to read and be asked to sign two consent forms. The first one is to participate in the study and to access their medical records from the GP and My Health Record (a secure online platform used in Australia used to store key healthcare information—this will facilitate pharmacists’ verification of clinical information when they make referral to GPs). The second consent will be used to release their Medicare Benefits Schedule (MBS) and PBS claims data from Services Australia.

Following recruitment, screening participants in the ***control*** group, if they are known patients with CKD (stages 1–4; based on self-report), will be provided with lifestyle advice and counselling on medications to avoid in kidney disease along with a Kidney Health Australia factsheet on ‘Looking after yourself with kidney disease’. All other control group patients will have their risk of developing CKD computed using the QKidney risk calculator,^38^ or based on blood pressure levels, if they have at least one of the known CKD risk factors. Participants will be advised of an appropriate action based on their calculated risk. All participants will be provided with lifestyle advice using a range of educational fact sheets, sourced from Kidney Health Australia resources, targeting their risk factors for CKD.

Following recruitment, participants in the ***intervention*** group will be divided into two groups.

Those with pre-existing CKD (Stages 1–4; based on self-report) and a serum creatinine (SCr) and eGFR measured within the last 3 months (accessed via My Health Record) will have their dispensing history and medication event summaries (My Health Record) reviewed to determine the presence of any medications considered problematic in kidney disease. Participants with inappropriate medication, doses or medication combinations based on their kidney function will have recommendations to adjust the doses of medications or cease contraindicated medications (QUM service) to their GP. Additionally, participants who, because of their kidney function, are eligible but not receiving potentially beneficial medications (eg, renin angiotensin system inhibitors or sodium glucose co-transporter 2 inhibitors) will have recommendations provided to their GPs to consider starting these medications. The pharmacists will be encouraged to upload their recommendations on the My Health Record platform as event summaries. Participants with no SCr/eGFR recorded in the last 3 months will have their kidney function determined using POCT followed by the QUM service.Participants with no prior history of CKD and at least one CKD risk factor will have their risk of developing CKD computed using the QKidney risk calculator. Participants who return with a moderate to high risk (>3% of developing moderate to severe CKD over 5 years) will have their kidney function determined using a POCT device for SCr and eGFR and will have their dispensing history reviewed to determine the presence of any medications considered problematic in kidney disease. Participants with any inappropriate dosages or contraindicated medications as per their kidney function will have recommendations to their GP to adjust the doses of medications/ceasing contraindicated medications or medication interactions (QUM service). Also, the recommendations may include introduction of potentially beneficial medications as highlighted above. The pharmacists will be encouraged to upload their recommendations on My Health Record as event summaries.

Screened participants in the intervention group are expected to attend a pharmacy session lasting between 20 and 45 mins with the trained pharmacist to assess and collect basic demographic and clinical/medical information (eg, height, weight, blood pressure, medications dispensed), and to apply the QKidney Risk assessment and POCT protocol and operating procedures. The time it takes for the overall procedure depends on the individual participant’s circumstances, such as the presence of pre-existing CKD or level of risk of developing it, type and number of medications involved as well as the need for screening referral to a GP. Similarly, participants in the control group will be expected to attend a pharmacy session at baseline lasting between 20 and 30 mins for the relevant risk assessment using the QKidney Risk tool and to provide relevant education and resources pertinent to their level of risk and risk factors for CKD.

Participants in the intervention group will be followed up by pharmacists/research project officers via phone or SMS (short messaging service) at 6 weeks to determine the status of the recommended follow-up with the GP and to re-advise GP review if participants have not yet made an appointment with their GP. All participants will be followed-up by pharmacists/research officers at 6 months and 12 months to determine the number of medications changed and new cases of CKD diagnosed (in participants with no prior history).

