## Methods

### Study setting and design overview

This study protocol is a multicentre, pragmatic, two-level cluster randomised controlled trial. The reporting of this protocol has been guided by the checklist outlined in the Standard Protocol Items: Recommendations for Interventional Trials (SPIRIT statement, online supplemental appendix 1).^31^

10.1136/bmjopen-2023-079110.supp1Supplementary data

Community pharmacies (clusters) are the unit of randomisation and screening participants are the unit of analysis. The project will be conducted in community pharmacies across three Australian states of New South Wales (NSW), Victoria (VIC), and Queensland (QLD) and later expanded to the Australian Capital Territory.

Community pharmacies will be selected from geographical groups of co-located postcodes to form clusters within the top 50 kidney disease hotspot areas identified by Kidney Health Australia.^14^ Co-located pharmacies within a cluster represent a local community that will all receive the same service model to reduce contamination bias. Pairs of clusters matched by characteristics such as location and socioeconomic status^32^ will be randomly allocated to the intervention or control groups. Objective geographical access is described using the Modified Monash Model (MMM). Consistent with the Australian Government Department of Health and Aged Care’s definition used in the Rural Health Multidisciplinary Training Program,^33 34^ the MMM for this study was broadly stratified into Metropolitan (MM1) and Rural (MM2–7) categories. Given there were no postcodes classified as ‘MM6 – Remote Communities’ or ‘MM7 – Very Remote Communities’ identified within the top 50 kidney disease hotspots, the Rural categorisation was constrained to MM2–5. The number of community pharmacies to be targeted is determined based on the respective population sizes of the states, with proportional pharmacy distributions across Metropolitan and Rural settings. Therefore, based on the population of the states and the percentage contribution of each state, a total of 122 community pharmacies will be recruited from the three states with 1:1 control:intervention allocation, representing 50 pharmacies from NSW (38 Metropolitan vs 12 Rural), 40 from VIC (30 vs 10) and 32 from QLD (20 vs 12). Given the proximity of some of the NSW pharmacies, we have expanded our recruitment to include pharmacies in the Australian Capital Territory.

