After the identification of the initial round of postcodes, these were stratified, and colour coded by the geospatial expert (VV) based on socioeconomic status and remoteness to ensure a balanced representation. The allocation into the intervention and control arms was randomised centrally at the University of Sydney by the project manager.

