#### Selection of community pharmacies

Community pharmacies within identified postcodes will be identified by triangulating sources such as ‘Yellow Pages’, ‘Google’ and the pharmacy finder in the Pharmacy Guild’s website. All identified pharmacies that are approved to dispense Pharmaceutical Benefits Scheme (PBS) medicines (Australia’s universal medicine subsidy programme); have a separate or private counselling area; accredited by an approved pharmacy accreditation programme; have FRED/Z dispensing software will be eligible to participate in the study. Of note, pharmacies without FRED/Z systems but have capacity for manual data entry may be considered for inclusion. Prior to participating in the trial, eligible pharmacies will be required to complete an online training and a baseline survey on existing practices on any screening and QUM services in different chronic diseases including CKD. All identified pharmacies will be contacted by the research team to participate in the study and, if consented to participate, provided with relevant training and onboarding information.

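### Participants are recruited after allocation by pharmacy staff who can be expected to know their arm, with no printed common rule for whom to approach, so the arms may differ in baseline CKD risk

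*Protocol article*

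**What the plan says.** The protocol article sets out this sequence.

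- **Allocation.** Study setting and design overview: "Community pharmacies (clusters) are the unit of randomisation and screening participants are the unit of analysis", and "The allocation into the intervention and control arms was randomised centrally at the University of Sydney by the project manager". The past tense places allocation before the participant recruitment described later.
- **Training by arm.** Selection of community pharmacies: "Prior to participating in the trial, eligible pharmacies will be required to complete an online training". Selection of pharmacists gives control pharmacists modules 1 to 3 and intervention pharmacists all four. Intervention pharmacists must also show competency with the point-of-care (POCT) device and receive extra training on it.
- **Device.** Intervention pharmacies have the POCT kit, rotated so that each has at least 6 months to reach 30 participants (Clinical protocol and recruitment procedure).
- **Recruitment.** Same section, text after figure 1: "The recruitment process involves the pharmacists discussing the study and confirming participant eligibility". All pharmacy staff are encouraged to help. "Promotional materials including flyers, posters and eligibility card for self-assessment will be provided to each participating pharmacy".
- **Eligibility.** Selection of participants eligible for screening: "Eligibility will be determined based on self-report by the prospective screening participant and based on the pharmacist’s judgement". The sentence goes on to limit that judgement to whether the person can make independent decisions about their health. Entry needs age 35 to 74 plus any one of a list of risk factors, including age 60 or over and current or former smoking.
- **Analysis.** The Data analysis plan specifies intention-to-treat. The first model contains group and region. The second adds age, gender, blood pressure, BMI, socioeconomic status and pharmacy location.

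**The concern.** In a cluster trial, randomisation protects the comparison of clusters. It protects the comparison of participants only if they are identified before allocation, or if the way they are chosen cannot depend on the arm. Here neither is stated. Staff approach people after allocation, and their training and equipment tell them which service those people will get.

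The criteria are broad enough that a pharmacy seeking about 30 people over 6 months has much room in whom it approaches. The two arms offer different services, so the reasons for approaching one customer rather than another may differ too. An intervention pharmacist might favour people for whom a creatinine result or medication review seems useful. The opposite is also possible: the article says the intervention session lasts 20 to 45 minutes depending on pre-existing CKD, risk level and medications, which could favour simpler cases.

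Both primary outcomes, new CKD diagnosis and change in problematic medications, depend on who is enrolled. A difference in case mix would be read as an effect of the service, or would hide one.

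**Working it through.** **1. Do recruiters know their arm?** No single sentence says so. It follows from three statements: training precedes participation, training content differs by arm, and only intervention pharmacies have the device and its training.

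**2. What could limit selection?**

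- Matching on location and socioeconomic status balances areas, not the individuals chosen inside each pharmacy.
- Intention-to-treat keeps enrolled people in their arm. It does not act on who was enrolled.
- The adjusted model covers age, blood pressure and BMI among the entry risk factors. It leaves out diabetes, cardiovascular disease, smoking and QKidney score.

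**3. The plan's sample size (Sample size section).** For 10% v 15%, 80% power and two-sided alpha 0.05, the pooled two-proportion formula gives 686 per arm.

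- Design effect = 1 + (30 − 1) × 0.05 = 2.45.
- Clusters per arm = 686 × 2.45 / 30 = 56.02, rounded up to 57. This reproduces the stated figure.
- 61 × 2 × 30 = 3,660, also as stated. Power with 61 per arm is about 83%.

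**4. Illustration of the stake.**

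From the article: 61 × 30 = 1,830 per arm; ICC 0.05; control diagnosis rate 10% (Sample size); 52% at moderate or high risk in the pilot (Background).

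Assumed: no true effect; 62% at moderate or high risk in the intervention arm; the diagnosis rate in low-risk people (two cases).

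SE = √(2.45 × [p₀(1 − p₀) + p₁(1 − p₁)] / 1830). With d = p₁ − p₀, the rejection rate is P(Z > 1.96 − d/SE) + P(Z < −1.96 − d/SE).

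*Case A, no diagnoses in low-risk people.*
- Rate in the moderate/high group = 0.10 / 0.52 = 0.192.
- p₁ = 0.62 × 0.1923 = 11.92%, so d = 1.92 points, or 38% of the 5-point target.
- SE = 0.0162 and d/SE = 1.19, giving a rejection rate of 22.2%.

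*Case B, 5% diagnosis rate in low-risk people.*
- Rate in the moderate/high group = (0.10 − 0.48 × 0.05) / 0.52 = 0.146.
- p₁ = 0.62 × 0.1462 + 0.38 × 0.05 = 10.96%, so d = 0.96 points, or 19% of the target.
- SE = 0.0158 and d/SE = 0.61, giving a rejection rate of 9.3%.

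Under Case A, other assumed shares give:

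| Intervention share | p₁ | Rejection rate |
|---|---|---|
| 57% | 10.96% | 9.3% |
| 62% | 11.92% | 22.2% |
| 67% | 12.88% | 41.8% |

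All these rates are for the unadjusted analysis of CKD diagnosis. No calculation was made for the medication outcome.

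**The case against.** The article is condensed. Figure 1, which shows the recruitment steps, is not available, and a training module taken by both arms covers identification and enrolment of participants. An invitation rule may exist there. That stands: one can say only that the printed procedure gives no such rule, not that none exists. What the article does fix is the order of events and who recruits.

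Several safeguards are partly in place. The study software manages potential participants, not only enrolled ones. The proportion screened is a process indicator, which needs a denominator. QKidney profiles and CKD risk factors are recorded at baseline and listed as outcomes, and an adjusted model is planned. These would help to reveal an imbalance and partly correct it. None of them governs whom staff approach.

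Three stronger readings are tempting and are not supported.

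- A reader might infer that pharmacists decide clinical eligibility. They do not: it is self-reported, and their judgement covers decision-making capacity only. The latitude lies in whom they approach.
- A reader might infer that a free blood test is advertised to draw higher-risk customers. The article mentions promotional material for every participating pharmacy and states no difference by arm. Testing of people without known CKD follows enrolment and depends on their QKidney result.
- A reader might take 22% as the trial's expected false-positive rate. The imbalance behind it is assumed, and the milder case gives 9%.

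**Conclusion.** The concern holds as a design weakness that should be addressed. The stated procedure lets staff who can be inferred to know their arm choose whom to approach after allocation, under broad criteria and towards a target of about 30 per pharmacy. The planned analysis removes the resulting bias only in part.

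The documents establish neither the size nor the direction of any imbalance. The 9% to 22% range rests on an assumed 10-point difference in risk share, no true effect, a normal approximation with pharmacies as clusters, and no covariate adjustment. It shows that a moderate difference in case mix would matter for a trial built to detect 5 points; it does not forecast one. The planned adjustment would lower these rates by an amount that cannot be derived from the documents.

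**What to change.** **Clinical protocol and recruitment procedure.**
- State one invitation rule for both arms, for example consecutive customers who meet the existing eligibility criteria, in set recruitment sessions.
- Log everyone approached, eligible, declined and enrolled in the existing study software.
- Keep flyers, posters and eligibility cards identical and arm-neutral.

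**Data analysis plan.**
- Add the baseline risk factors to the adjusted model: diabetes, cardiovascular disease, smoking and, for participants without known CKD, QKidney score. The article lets control participants' risk be based on blood pressure instead of QKidney, so the score should be recorded in both arms if it is to serve as a covariate.
- Report approached-to-enrolled ratios by arm.

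**Two limits.** Invitations should not be restricted to a list drawn from dispensing records. Such a list would miss people who qualify through smoking, obesity, family history or Aboriginal and Torres Strait Islander origin, and so would change the trial population. Arm-specific information needed for consent, such as the finger-prick test, should not be withheld.

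**Cost.** Pharmacists lose some freedom in whom they approach, logging adds a small burden, and recruitment may be slower. People already enrolled cannot be re-selected, so for them only the analysis changes help.

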**Methods and analysis:**

This study is a multicentre, pragmatic, two-level cluster randomised controlled trial which will be conducted across different regions in Australia. Clusters of community pharmacies from geographical groups of co-located postcodes will be randomised. The project will be conducted in 122 community pharmacies distributed across metropolitan and rural areas. The trial consists of two arms: (1) Control Group: a risk assessment using the QKidney CKD risk assessment tool, and (2) Intervention Group: a risk assessment using the QKidney CKD plus Point-of-Care Testing for kidney function markers (serum creatinine and estimated glomerular filtration rate), followed by a QUM service. The primary outcomes of the study are the proportion of patients newly diagnosed with CKD at the end of the study period (12 months); and rates of changes in the number of medications considered problematic in kidney disease (number of medications prescribed at inappropriate doses based on kidney function and/or number of nephrotoxic medications) over the same period. Secondary outcomes include proportion of people on potentially inappropriate medications, types of recommendations provided by the pharmacist (and acceptance rate by general practitioners), proportion of people who were screened, referred, and took up the referral to visit their general practitioners, and economic and other patient-centred outcomes.

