### Trial objectives

The overarching aim is to evaluate the effectiveness of pharmacy-led screening in enhanced detection of previously unknown CKD cases and QUM intervention in optimising medication use for patients with CKD. Specifically, the aim is to:

Determine the effectiveness of a community pharmacy-led screening using POCT on the detection of previously undiagnosed CKD compared to risk assessment alone.Evaluate the impact of community pharmacy-led QUM service informed by POCT in improving the appropriateness of medication use in people with CKD.Investigate the effectiveness of community pharmacy-led CKD screening and QUM service on long-term economic benefits and humanistic outcomes such as health-related quality of life, and consumer well-being and satisfaction.

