### Hypotheses

We hypothesise that the use of a POCT with CKD risk assessment (POCT+QKidney Risk Assessment: Intervention Group) in community pharmacies will result in (1) a significantly improved detection of previously unknown CKD cases, and (2) reduced use of potentially inappropriate medications when compared with CKD risk assessment alone (QKidney Risk Assessment: Control Group).

Other hypotheses related to the primary hypothesis are that the Intervention Group will be associated with a statistically significant increase in the proportions of those who are referred to the GP, take up referral with the GP, are newly diagnosed with CKD compared with the Control Group.

Additionally, the incorporation of POCT in conjunction with the QKidney Risk Assessment will lead to enhanced utilisation of kidney beneficial medications (ie, those that slow kidney disease progression), a long-term economic benefit and improved humanistic outcomes.

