### Outcomes

#### Primary outcome measures

Proportion of patients newly diagnosed with CKD at the end of the study period.Changes in the number of medications considered problematic in kidney disease (number of medications prescribed at inappropriately high dose, number of contraindicated medications or detrimental drug interactions).

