#### Secondary outcome measures

Proportion of screening participants with inappropriate medications (number of medications at inappropriate high dose based on the kidney function and number of contraindicated medications).Proportion of eligible participants without potentially beneficial medications (eg, renin angiotensin system inhibitors or sodium glucose co-transporter 2 inhibitors).The number and characteristics of proposed medication adjustments recommended by pharmacists and acceptance rates by GPs.Proportion of participants with CKD risk factors.Proportion of participants screened (process indicator).Participants’ QKidney risk profiles.Percentage of participants referred to their GP.Percentage of participants who take up referral with their GP.Number of hospitalisations due to medication-related events.Cost effectiveness.Health-related quality of life, consumer well-being and satisfaction.

Both the intervention and control group participants will be followed-up by the project officers/pharmacists at 6 and 12 months to determine if they have had any additional blood tests, and changes to their medications, and hospitalisations.

Primary outcomes will be determined based on data collected from GPs. Health-related quality of life and overall participant well-being will be measured using the EuroQoL-5D-5L, which consists of a descriptive system and a Visual Analogue Scale.^39^ The EQ-5D-5L is scored on a 0–1 utility scale, where 0=death and 1=full and complete health. Unit values will be informed by Australian population estimates.^40^ A minimally important difference of 0.07 (7%) change in utility on the EQ-5D-5L scale is considered to be clinically meaningful.^41^

Screening participants’ satisfaction with the service and willingness to pay for the service will be determined by a telephone questionnaire, which will include items relating to service approval (5-point Likert scale); and open-ended questions to elicit reasons for approval and satisfaction ratings. Screening participants’ willingness to pay for the service will also be determined including the maximum amount. Satisfaction of pharmacists (at midtrial and end of trial) with the screening and QUM services will be assessed using electronic surveys. The GPs involved in the care of the participants will also be sent a survey at the end of the trial to determine their satisfaction and any effects on their practice.

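### Minor: for participants with self-reported CKD the arm labels do not describe the care compared, so their medication result is not a contrast with risk assessment alone

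*Protocol article*

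**What the plan says.** - **Labels.** The Abstract (Methods and analysis) gives the arm as "Control Group: a risk assessment using the QKidney CKD risk assessment tool". The Hypotheses section predicts "reduced use of potentially inappropriate medications when compared with CKD risk assessment alone (QKidney Risk Assessment: Control Group", and labels the intervention arm as POCT plus QKidney.
- **Control procedure.** Under Clinical protocol and recruitment procedure, controls who report CKD stages 1–4 "will be provided with lifestyle advice and counselling on medications to avoid in kidney disease" and receive a factsheet. The remaining controls have their risk computed with QKidney or judged from blood pressure. All participants receive lifestyle fact sheets. The later summary of the control visit describes a session "lasting between 20 and 30 mins for the relevant risk assessment using the QKidney Risk tool", with education, and makes no distinction by known CKD.
- **Intervention procedure.** Participants with pre-existing CKD have their medicines reviewed and receive the QUM service. POCT is used only when no creatinine and eGFR result from the last three months exists. QKidney appears only in the pathway for those with no prior CKD, who go on to POCT and review if their risk is moderate or high.
- **Outcome.** The second primary outcome counts problematic medicines, including the "number of contraindicated medications or detrimental drug interactions". On data source: "Primary outcomes will be determined based on data collected from GPs".
- **Aim.** The second objective is to "Evaluate the impact of community pharmacy-led QUM service informed by POCT in improving the appropriateness of medication use in people with CKD". It names no comparator, so the Hypotheses section supplies it.

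**The concern.** The word alone in a formal hypothesis will be carried into the conclusion. For participants with known CKD the named control component (QKidney) is absent and an unnamed one (counselling on medicines to avoid) is present. That counselling has the same target as a primary outcome, unlike the general lifestyle advice that everyone receives. A small or null difference in this stratum could then be reported as a QUM service no better than risk assessment, when it was in fact compared with medication counselling. If the counselling works, the reported contrast understates the benefit over risk assessment alone. The other primary outcome is hardly touched, since follow-up looks for new CKD in those with no prior history.

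**Working it through.** **1. Is the stratum in the trial?** Yes. Selection of participants eligible for screening excludes only kidney failure and kidney replacement therapy, so stages 1–4 can enrol.

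**2. Care by stratum, from Clinical protocol and recruitment procedure.**

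| Stratum | Intervention | Control |
|---|---|---|
| Known CKD (self-report) | Medication review and QUM; POCT only if no recent result; no QKidney listed | Lifestyle advice, medication-avoidance counselling, factsheet; no QKidney |
| No known CKD | QKidney; POCT, review and QUM if risk is moderate or high | QKidney or blood-pressure-based risk, action advice, fact sheets |

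The labels in the Abstract and Hypotheses fit the second row approximately and the first row in neither arm.

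**3. Scale of any narrowing.** The documents give neither the share with known CKD nor the counselling effect. Assume 1, 3 or 6 known-CKD participants among the planned 30 per pharmacy. A 1-point reduction due to counselling narrows the known-CKD contrast by 1 point and the pooled contrast by the share: 1/30 = 0.03, 3/30 = 0.1 or 6/30 = 0.2 points.

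**4. Check of the plan's design effect.** Sample size gives ICC 0.05 and 30 per cluster, so the design effect is 1 + 29 × 0.05 = 2.45. For diagnosis (10% vs 15%, 80% power), 686 × 2.45 / 30 = 56.02, i.e. 57 clusters per arm, as stated. For medicines (32.3% vs 17.5%, 90% power), 178 × 2.45 / 30 = 14.5, i.e. 15 per arm. The plan's 19 is on the safe side, and this point does not depend on it.

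**5. Power if the control rate falls.** Illustration only: the intervention rate is held at 17.5%, the test is two-sided at 0.05, and all 30 per cluster contribute.

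| Control rate, whole arm | Power, 19 per arm | Power, 61 per arm |
|---|---|---|
| 32.3% (plan) | 0.96 | 1.00 |
| 30.0% | 0.89 | 1.00 |
| 27.5% | 0.74 | 1.00 |
| 25.0% | 0.51 | 0.94 |
| 22.5% | 0.27 | 0.68 |

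If 20% of participants had known CKD, a fall in the whole arm to 30.0% (2.3 points) would need a counselling effect of 2.3 / 0.2 = 11.5 points in that stratum. So a narrower contrast does cost power, though at these assumed shares and with 61 pharmacies per arm the pooled cost is small.

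**6. Precision of an estimate in known CKD.** The Sample size proportions stand in for the count outcome, with 61 pharmacies per arm and m participants each:

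half-width = 1.96 × √[(0.323 × 0.677 + 0.175 × 0.825) × DE / (61m)], with DE = 1 + (m − 1) × 0.05

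| m | n per arm | DE | 95% half-width (points) |
|---|---|---|---|
| 1 | 61 | 1.00 | 15.1 |
| 3 | 183 | 1.10 | 9.2 |
| 6 | 366 | 1.25 | 6.9 |
| 30 (pooled) | 1830 | 2.45 | 4.3 |

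**The case against.** The strongest reply is that these are arm labels, not specifications. In the Hypotheses sentence, alone can be read as meaning without POCT, and the intervention label is just as short: it omits the QUM service and does not fit known CKD either. The procedure section states the control care openly, so no site would act differently. An abstract is expected to condense. Other controls also get advice and fact sheets, so alone is not literally exact for them. All of this stands. It keeps the point minor, and it is why both labels need rewording, not just the control one.

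Two further replies also have force. Control pharmacists do not take the QUM training module (Selection of pharmacists) and the outcome rests on GP data, so any counselling effect may be small. Covariates and subgroup displays are often left to an analysis plan. Here, though, the Data analysis plan already fixes a covariate list, and known-CKD status, which decides the care given in both arms, is not on it.

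A reader might infer more than the documents support:
- *That the comparison is biased or the co-intervention concealed.* The counselling is part of the described control care, and randomised arms compared as delivered give a valid contrast.
- *That the comparator is wrong for the whole medication objective.* That objective concerns people with CKD, not only those who report it at recruitment. The Abstract frames the hypothesis for people at risk of or living with CKD, and the QUM service also reaches moderate- and high-risk participants with no prior history. Known-CKD controls are one part of that population, of unstated size.

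**Conclusion.** The point holds as a minor one about labelling and interpretation. In participants with self-reported CKD the trial compares medication review and QUM (with POCT if needed) with lifestyle advice plus medication-avoidance counselling. Neither arm is QKidney-based there, so a medication result in this stratum cannot be reported as a gain over risk assessment alone.

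If control counselling has a beneficial effect, it narrows the contrast and lowers power. The direction rests on that condition, and the size cannot be derived from the documents. The 0.03 to 0.2 points per point of counselling effect rest on assumed known-CKD shares of about 3% to 20%. The power and precision figures also use proportions in place of a count outcome.

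**What to change.** 1. In the Abstract, the Hypotheses and the summary of the control visit, state both arms by stratum. Known CKD: QUM, with POCT if needed, versus lifestyle advice and medication-avoidance counselling. No known CKD: QKidney, plus POCT and QUM if risk is moderate or high, versus QKidney or blood-pressure-based risk assessment with education.
2. Word the medication conclusion to match, so that a claim against risk assessment is not extended to participants with known CKD.
3. For the medication outcome, add known-CKD status to the adjusted model in the Data analysis plan and report the effect descriptively by that status, with the numbers in each arm and no interaction test.

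The cost is wording plus one covariate. The status is established at recruitment in both arms because it decides the pathway, so no new data collection or change in sample size is needed. The limit should be stated with the result: the known-CKD estimate would carry an interval of roughly ±7 to ±15 points under the assumed numbers, against about ±4 pooled, and it cannot separate effective control counselling from an ineffective QUM service.
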